**RESEARCH PROJECT**

**3 - INTRODUCTION**

Studies show that dissatisfaction with stained or darkened teeth varies from 18 to 53%, which is observed in approximately 40% of individuals with aged between 16 and 54 years. In this sense, bleached teeth can influence quality of life as they improve satisfaction with dental appearance.1 There are numerous treatments for intrinsic and extrinsic pigmentation of teeth, including home bleaching, in-office bleaching, dental restorative and even treatment prosthetic.2

In-office dental bleaching is a widely used procedure and is usually performed with high concentrations of hydrogen peroxide (35% to 38%). 3 This whitening agent, in turn, acts mainly through the oxidation of organic compounds and the released O2 penetrates into the dentinal tubules and acts by breaking the organic pigment macromolecules into hydroxyl groups that are lightly colored (free radicals) .4 When the bleaching passes the saturation point, the peroxide acts on other compounds that have carbon chains, such as enamel matrix proteins. At this time, the loss of physiological organic structures becomes very rapid and is converted into carbon dioxide and water, which leads to an increase in dental microporosity.5

Although deleterious effects occur on the enamel microstructure, the painful sensitivity derived from tooth bleaching is the result of a reversible pulpitis.6 Reactive oxygen species (ROS) released in chemical oxidation reactions can easily pass through the enamel and dentin and reach the pulp of the tissue causing structural damage and inflammatory reactions.7

To minimize the side effects of bleaching treatment, the use of desensitizing and remineralizing agents before, during or after whitening has been used clinically. These agents include fluoride, calcium, potassium nitrate, nanohydroxyapatite, potassium oxalates, strontium chloride, low-level lasers, etc. 8,9,10,11 Despite the vast information available, there are still controversies about the effectiveness of these desensitizing agents during and after bleaching treatment in preventing the side effects of tooth whitening. Clinical trials have shown the incidence of tooth sensitivity even when these products are applied, this condition may be associated with structural changes in the enamel and dentin.12,13

In 1935, Grossman listed the basic requirements that a desensitizing material should have, which are still valid today: non-toxic material, non-irritating to the pulp, easy to apply and spread, fast performance and should not cause tooth discoloration.14 In view of the possible materials for this purpose, strontium chloride could be a good option for this purpose. Strontium chloride was the first material with obstructive action of dentinal tubules to be used in a desensitizing toothpaste.15 So that strontium salts can replace the hydroxyapatite calcium due to the chemical similarity of these elements, obliterating the dentinal tubules and favoring the tissue remineralization.16

Low-level laser therapy (LLLT), with wavelengths ranging from 630, 780, 810, 830 or 900 nm, has also been increasingly used in medicine and dentistry due to its analgesic, anti-inflammatory and biostimulative effects.17 These properties, suggest that LLLT may be able to mitigate the damage and inflammation induced by office bleaching products in pulp tissues, and thus may eventually reduce the risk and intensity of sensitivity in bleached teeth.18

Although there are numerous therapeutic applications for lasers, their effectiveness in improving and preventing pain is still controversial.17 The same occurs with treatments aimed at applying strontium chloride-based desensitizers.15 Accordingly, there is a need of clinical studies that can elucidate the association of these two forms of treatment for the action of tooth bleaching on postoperative sensitivity, considering that each of the two methods of pain prevention acts through a specific mechanism: neuronal response or tubule obliteration dental.

**4 - JUSTIFICATION**

The most common adverse effect resulting from whitening treatment is dentinal sensitivity.19 More recently, the sensitivity caused by tooth bleaching has been explained as the result of an acute, transient, reversible pulpitis.20 The rapid penetration of peroxide towards the pulp causes changes in osmolarity and the release of factors derived from cells such as ATPs (adenosine triphosphates), neuropeptides and prostaglandins, which sensitize pulp nociceptors. In addition, the inflammatory process can induce vasodilation and increase pulp blood flow and prostaglandins.21

More than 70% of patients undergoing dental bleaching treatment complain of postoperative sensitivity.22 Therefore, recent research has reported the use of several remineralizing bioactive agents, protein precipitates, dentinal tubule obliterating compounds and the use of low-level lasers, aiming to prevent the painful effects of tooth bleaching treatment.23,24,25

Strontium chloride has an atomic radius slightly greater than calcium and readily replaces calcium minerals, leading to the formation of a calcium-strontium apatite complex [Ca6Sr4(OH)2] on the surface of the apatite crystals which slows down dissolution hydroxyapatite acid.26,27 And studies have shown that strontium has shown a high affinity for dentin and apatite.28

On the other hand, the action of LLLT in controlling the inflammatory process has brought benefits to bone regeneration and wound healing treatments, reducing pain and edema.29 The most accepted explanation for improving tissue repair after the application of therapeutic lasers is that these devices provide energy to the target cells, which can be used to stimulate their membrane or organelles. The laser radiation is absorbed through cytochromes in the mitochondria and converted into energy by the adenosine-5'-triphosphate (ATP) cells, which acts on protein synthesis and the acceleration or stimulation of cell proliferation.30

LLLT has been successfully applied in the treatment of dentin hypersensitivity, by inducing changes in the nerve transmission network within the dental pulp. Furthermore, the effect is biostimulative, as it stimulates the neoformation of secondary dentin and, thus, promotes the physiological obliteration of dentinal canaliculi and stimulates the formation of endorphins in the synapse of nerve endings.31 LLLT is being used in several areas of health and it can promote to the injured tissues some level of regeneration. This therapy results in analgesic, anti-inflammatory and biostimulatory effects.32

GaAlAs (gallium-aluminum-arsenide) diode lasers have a reduction in the effects of dentin hypersensitivity through the induction of neural transmission within the dental pulp, stimulating the physiological functions of cells, with pulp tissues being less damaged or inflamed to external aggressions.33 However, there is no clinical evidence of the effectiveness of LLLT in the sensitivity resulting from the bleaching treatment.

The present clinical study aims to use a method known as split-mouth. Some advantages can be highlighted when comparing the split-mouth design with parallel studies, among them, the need for a smaller sample size.34.34 Furthermore, in this study format, it is possible to minimize inter-individual variables, since the participating subjects they serve as their own controls. According to Smaïl-Faugeron et al., This decrease in inter-individual variability increases the power of the study.35

In order to carry out an adequate investigation of pain prevention, appropriate assessment methods are needed. Most instruments that assess pain are one-dimensional measures of intensity. The most commonly used instrument is the Visual Analog Scale (VAS), which, for young individuals, has a high index of validity and reliability.36 Another widely used method is the daily questionnaire for verbal description of pain. However, one of the reasons that makes pain measurement difficult is subjectivity, since the painful experience is described as something multifactorial and subjective. Given this and aiming to minimize the subjective factors of the described methods, this study aims to use both the VAS and the daily questionnaire to obtain the data.

Thus, it is observed that both strontium chloride and low-level laser therapy have their action in the activity of transmission of the nervous impulse, being of great relevance for the resolution or alleviation of painful symptoms caused by whitening agents in dental practice. In this context, clinical trials are of great value in the literature for a better investigation of these problems, as it is the type of study that provides the highest level of scientific evidence regarding the effectiveness and safety of interventions. When performed correctly, it allows the production of results with less possibility of bias.

**RESEARCH PROJECT**

**5 – AIMS**

To clinically evaluate the effect of low-level laser therapy (LLLT) associated with strontium chloride 10% (SC), in the control of postoperative painful sensitivity caused by dental bleaching in the office. The null hypothesis tested in the present study will be:

H0 - There will be no difference in postoperative sensitivity between the bleached groups in the face of the association of two treatments with desensitizing action (LLLT / SC), when compared to the use of SC10% and LLLT in isolation in the different evaluation periods.

**6 – METHODOLOGY**

## **6.1. Ethical aspects**

This research project followed the guidelines of “*CONSORT”* (Consolidated Standards of Reporting Trials). The research volunteers will be duly clarified and informed about the risks, methods and objectives of this project, and it will be necessary to sign the informed consent form - TCLE (Annex I), in accordance with the Helsinki declaration.

All information to be collected will be for scientific use only and the identity of the volunteers will be preserved. Participation in the study can be canceled and the consent form withdrawn at any time during the research, ensuring the confidentiality of the volunteer even in case of treatment abandonment.

## **6.2. Sample selection**

Fifty patients aged 18 to 31 years of both sexes will be selected for the study. The following inclusion and exclusion criteria were used for sample selection (Table 1).

**Table 1:** Inclusion and exclusion criteria.

| - **INCLUSION CRITERIA** | **x EXCLUSION CRITERIA** |
| --- | --- |
| - Good oral hygiene; - Absence of active caries lesions; - Never having undergone previous bleaching therapy; - Do not present tooth hypersensitivity; - Non-smoking; - Not being pregnant; - Have at least 28 teeth in the oral cavity. | - Presence of periodontal disease; - Dental cracks or fractures, restorations and prostheses on anterior teeth - Extensive molar restorations; - Gastroesophageal disorders; - Severe internal dental darkening; - Exposure in anterior and/or posterior teeth; - Orthodontic treatments. |

All participants will be submitted to prophylaxis performed with a rubber bowl and pumice stone seven days before the beginning of the study and will receive oral hygiene kits, for standardization of a toothpaste that does not have a desensitizing action and does not contain fluoride, in order to mitigate possible interference. in the evaluation of this study, the Kit will consist of a toothbrush (Oral B, Bristle Indicator, São Paulo, SP, Brazil) and a toothpaste (My First Colgate®, Colgate-Palmolive Company, SP, Brazil), under guidance for use three times a day.

## **6.3. Study design**

The clinical study will be controlled, double blind, randomized and will use the split mouth model. For the determination of the groups, a randomization process will be carried out that will determine the different treatment to be applied to the different sides (right or left) of the quadrants, including the central incisors, lateral incisors, canines and premolars of each hemi-arch. Thus, the four groups to be studied will be formed at random.

All groups will be submitted to the office whitening treatment with 35% hydrogen peroxide (Whitness HP, FGM, Joinville, SC, Brazil). LLLT and the application of the desensitizer containing strontium chloride 10% will occur in all three sessions of the bleaching treatment, considering the seven-day interval between sessions.

The dental elements of the G1 and G2 groups will receive 10% strontium chloride (SC) (Sensodyne Original- FGM, Joinville, SC, Brazil) on the buccal surfaces with an active rubber cup for 10 minutes following the guidelines of the manufacturer, and the G2 group will also receive the application of LLLT (Photon Laser III visible infrared therapeutic / DMC Equipment, São Carlos, SP, Brasil, Ltda.), with the light mission at the apical and cervical points of the dental element, while for G1 and G3 the laser tip will only be positioned on the dental surface, without emitting light, mimicking the application of LLLT. The G3 group will also receive the placebo gel application, under the same conditions as strontium chloride. And finally for G4 the placebo gel will be applied in association with LLLT in the hemiarchate.

**Table 2.** Division of groups, bleaching treatment, desensitizing treatments.

| **GROUPS** | **BLEACHING TREATMENT** | **DESENSITIZING TREATMENTS** |
| --- | --- | --- |
| **G1** | Whiteness HP 35% FGM | Desensibilizer Sensodyne Original +  Mimicking the application of LLLT |
|
| **G2** | Desensibilizer Sensodyne Original + |
| Laser application - Photon lase III DMC |
| **G3** | Placebo gel+ Mimicking the application of LLLT |
|
| **G4** | Placebo gel+ |
| Laser application - Photon lase III DMC |

## **6.4. Randomization**

The randomization process will be carried out using the Bioestat 5.0 software (Civil Society, Mamirauá, Pará, Brazil), which will use a computer generated random table. This process will take place in two stages. The first randomization process will be carried out after the selection of participants in order to distribute them in two large groups, that is, the first with patients who will be submitted to strontium chloride therapy (G1 - G2), and the second with patients submitted to the use of placebo gel (G3 - G4), in order to avoid contamination between the arches by the desensitizing agents employed. The second randomization will be carried out to allocate the different treatments in the hemiarchies within each large group, determining the groups: G1; G2; G3 and G4. The volunteers' medical records were coded for sample randomization.

**Flowchart 1.** Study design.

[figure not shown]

**6.5. Blinding**

The investigation will have only one investigator, not participating in the randomization and without knowledge of the interventions applied in the groups for the statistical analysis of painful sensitivity. The volunteers evaluated in the research will also not be aware of which hemiarchy strontium chloride will be applied, associated or not with LLLT, characterizing the double-blind study. LLLT in groups G1 and G3 will be mimicked. The laser tip will only be positioned on the dental surface, with no light emitted. The noise emitted by the laser equipment during light emission will be simulated using the iTalk Recorder application (Griffin Technology, Nashville, Tennessee, USA) for the iPhone 6 smartphone (Apple®, Cupertino, CA, USA). Groups G3 and G4 will also be subjected to the application of a placebo gel to mimic the application of the dentin desensitizer. Both products will be placed in identical containers so that patients do not identify themselves in relation to the application of the product.

## **6.6. Tooth bleaching**

All groups will receive the office whitening treatment. Before whitening, prophylaxis will be performed on teeth with pumice (Asfer, São Caetano do Sul, SP, Brazil). Then, a gingival barrier will be made with Top Dam light-curing resin (FGM, Joinville, Brazil). A 45-minute application of 35% hydrogen peroxide gel (Whitness HP, FGM, Joinville, SC, Brazil) will be performed in each of the 3 sessions, with an interval of 7 days between them, on the buccal surface of the incisors , canines and premolars of the upper and lower arches. At the end of the third whitening session, the whitened surfaces will be polished with felt disc (Kota, São Paulo, Brazil) and diamond paste (Diamond R, FGM, Joinville, Brazil).

**6.7. Strontium Chloride**

Groups G1 and G2 will be subjected to the application of 10% SC based desensitizer (Sensodyne Original-FGM, Joinville, SC, Brazil), on the buccal surfaces of incisors, canines and premolars with the aid of a Microbrush applicator ( Microbrush, 3M ESPE, São Paulo, Brazil) for 10 min. Then, a rubber bowl mounted on a low speed handpiece will be used to rub the desensitizing gel on the teeth for 10 seconds on each tooth, as specified by the manufacturer.

**6.8. Laser therapy**

LLLT will be performed in groups G2 and G4 through the application of the laser with a spectrum of infrared light with a wavelength of 808 nm with its active medium AsGaAl, at two points on the buccal surface of the incisors, canines and premolars, one being point in the cervical region and one point in the apical region. It will be applied at each point 60 J / cm², for 16 seconds, using the Photon Laser III therapeutic visible infrared / DMC Equipamentos, São Carlos, SP, Brasil, Ltda.

## **6.9. Assessment of painful sensitivity**

The daily assessment of painful sensitivity will be performed using a modified visual analog scale (VAS), based on the following pain scores: absent (0); mild pain (1); moderate pain (2) and severe pain (3), which will be delivered to the volunteers to be measured during the 21 days of treatment, based on the perception of individual pain in each patient in the right and left dental hemi-arches.

**6.10.4. Statistical analysis**

The sensitivity values reported by the volunteers will be tabulated in an Excel spreadsheet (Microsoft Windows 2010) and analyzed using the BioEstat.® program Considering the non-parametric data of this study, the intragroup analysis will be performed from the Friedman and the intergroup by the Wilcoxon and Mann-Whitney test. For all analyzes, significance levels of 5% will be considered.

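### With no primary outcome or defined evaluation period and 5% for every test, the chance of falsely rejecting H0 is well above 5%

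*Protocol*

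**What the plan says.** Protocol section 6.9 has each volunteer score pain on a four-level scale, from 0 (none) to 3 (severe), separately for the right and left hemi-arch, "to be measured during the 21 days of treatment". Section 4 adds a second instrument: "this study aims to use both the VAS and the daily questionnaire to obtain the data". Neither instrument is ranked above the other.

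The null hypothesis in section 5 is that the combination of laser and strontium chloride does not differ in postoperative sensitivity, "when compared to the use of SC10% and LLLT in isolation in the different evaluation periods". In the group labels of section 6.3 this is G2 against G1 (two sides of the same patients) and G2 against G4 (different patients).

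Section 6.10.4 states that "the intragroup analysis will be performed from the Friedman and the intergroup by the Wilcoxon and Mann-Whitney test", and then: "For all analyzes, significance levels of 5% will be considered". The protocol names no primary outcome, primary time point, summary score or order of testing, and no adjustment for multiple tests. It does not say what the evaluation periods are.

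**The concern.** As H0 is worded, a difference in either comparison in any period counts against it, and each such test carries its own 5%. The 5% is then the error rate of one test and not of the trial's conclusion. Because the periods are undefined, they could also be chosen after the scores have been seen. A few significant periods could be read as a benefit of combining the two treatments, with a chance of error several times the stated level.

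**Working it through.** The protocol gives no overall error rate to reproduce. Its sample size ("Fifty patients aged 18 to 31 years of both sexes will be selected for the study") comes with no effect size or power.

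**Inputs from the protocol:** two comparisons in H0 (section 5); 21 daily scores of 0–3 per hemi-arch (section 6.9); three sessions seven days apart (sections 6.3 and 6.6); Wilcoxon and Mann-Whitney tests at 5% (section 6.10.4).

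**Assumptions, not in the protocol:** 25 patients in each of the two sets; two-sided tests; correlation of 0.5 between the two sides of a patient; correlation between days of 0 to 0.9; the share of sides with pain on each day.

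**Step 1, number of tests of H0.**
- Three weekly periods: 2 × 3 = 6.
- Every day: 2 × 21 = 42.

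**Step 2, reference value for independent tests,** 1 − 0.95^k:
- k = 6: 26.5%
- k = 14: 51.2%, the first k above one half
- k = 42: 88.4%

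Daily scores in one mouth are not independent, and tests on days with little pain reject less often than 5%, so these values are only a reference.

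**Step 3, simulation with no treatment effect,** 2,000 trials per setting, tie-corrected normal approximations. The entries give the chance of at least one p < 0.05, with the range taken over the between-day correlations. For 6 tests the weekly score was either that of the session day (days 1, 8 and 15) or the highest of the week.

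| Share of sides with pain | 6 tests, session day | 6 tests, weekly highest | 42 daily tests |
| --- | --- | --- | --- |
| 70% every day | 20.0–27.8% | 16.4–25.4% | 43.0–87.9% |
| 40% every day | 17.1–27.4% | 15.4–26.4% | 41.7–85.6% |
| Falling after each session: 70, 40, 20, 10, then 5% | 16.6–25.9% | 16.2–25.6% | 43.8–71.8% |
| Falling fast: 70, 30, 10, 3, then 1% | 18.5–27.0% | 18.4–26.3% | 36.3–54.1% |

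Overall this is about 15–28% for 6 tests and 36–88% for 42. The 42-test figure drops below one half when days are very highly correlated (about 0.9, exchangeable) or when pain is near zero on most days.

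**Step 4, the same two comparisons on one summary score.**
- Both tested at 5%, either one sufficing: 1 − 0.95² = 9.75% if independent, still above 5%.
- Holm (smaller p-value against 0.025, the other against 0.05): at most 5%.
- Both required at 5%: a false claim needs a test of a truly null comparison to reject, so at most 5%.

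**Step 5, what error control costs.** The standardised difference detectable with 80% power, by normal approximation, is (z for 1 − α/2 + 0.842) × √(2/25) for unpaired groups. With √(1/25) it holds for pairs correlated 0.5.

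| Level per test | Unpaired | Paired |
| --- | --- | --- |
| 0.05 | 0.79 | 0.56 |
| 0.025 | 0.87 | 0.62 |
| 0.05/42 = 0.0012 | 1.15 | 0.82 |

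Adjusting over 42 days asks for much larger effects than adjusting over two comparisons.

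**The case against.** The strongest reply is that daily collection is not daily testing. Section 6.9 says when scores are recorded, section 6.10.4 does not say which days enter the tests, and three sessions a week apart make three weekly periods a natural reading. This stands: testing on every day is an inference, so the 42-test range is conditional. The weekly reading still gives 15–28%.

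A second reply is that periods and multiplicity are often settled in a statistical analysis plan, which is not at hand. That is fair for the detail. But the protocol does more than leave the matter open: it sets 5% for all analyses and states a hypothesis over several periods without a primary outcome.

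A reader might go further and infer any of the following, which the protocol does not support:
- **That a chance rejection is more likely than not.** Even with 42 tests the range runs from 36%, and with 6 tests it stays below 30%.
- **That 84 or 126 daily tests are at issue.** Those counts take in group pairs outside H0, and the protocol does not say that all pairs are tested.
- **That each daily test is also weak.** No effect size is stated from which to judge this. For 70% against 40% of sides with pain on one day, the paired Wilcoxon test has about 76–99% power at side-to-side correlations of 0.3 to 0.8. Power is low on low-pain days (20% against 10%: about 15–23%), but those days also add few false positives.

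**Conclusion.** The point holds. With no primary outcome, undefined periods and an unadjusted 5% for each test, the chance of falsely rejecting H0 exceeds 5% on every reading computed: about 15–28% for three weekly periods, and about 36–88%, so possibly above one half, if each day is tested. The ranges depend on the assumed 25:25 split, two-sided tests, correlations and pain time courses. That the rate is above 5% follows from the wording of H0 together with the 5% rule. The counts leave out the daily questionnaire, which could add further tests if it were analysed in the same way.

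**What to change.** Amend sections 5 and 6.10.4 before the data are analysed.

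1. Name one primary outcome per hemi-arch, for example the sum of the daily 0–3 scores over the 21 days, or the mean of completed days where some are missing. Say that the questionnaire is secondary.
2. Test H0 on that outcome only: Wilcoxon for G2 against G1, Mann-Whitney for G2 against G4.
3. State the joint rule. If the claim is that the combination beats each single treatment, require both comparisons at 5%. If either one suffices, use Holm.
4. Define the evaluation periods, and report daily and weekly scores as secondary, either descriptively or Holm-adjusted.

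This takes a few sentences, and no new data, patients or tests. The cost is that day-specific p-values are no longer confirmatory. Requiring both comparisons also lowers the chance of a positive conclusion, and Holm asks for a somewhat larger effect from the first comparison. A sum treats the steps between pain levels as equal. Another single summary, such as the peak score, would control the error equally well if it is fixed in advance.
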